# Community and Academic Synergy for Cancer Survivorship Care Delivery Enhancement (Project CASCADE): a study protocol for a pragmatic, stepped-wedge, cluster-randomized trial in Texas primary care community health centers

**DOI:** 10.1186/s12875-025-03108-1

**Published:** 2025-12-27

**Keywords:** Cancer survivorship, Care delivery, Primary care, Community health centers

## Abstract

**Background:**

In the United States, over 18 million individuals are living with cancer. The majority of these cancer survivors also manage other chronic conditions and receive care from multiple specialists, including oncology, cardiology, and primary care clinicians. However, it remains unclear who holds primarily responsibility for coordinating their care across specialties. Because of its generalist nature, primary care is uniquely suited to deliver whole-person and coordinated care for all conditions for cancer survivors. However, primary care teams experience many challenges delivering high-quality survivorship care. While integrating care for all conditions including cancer is a core principle of high-quality primary care, few survivorship care delivery interventions have been developed and tested among patients with a history of cancer in primary care panels of community health centers (CHCs). These under- and uninsured cancer survivors experience disproportionately worse health outcomes and often rely solely on CHCs for consistent health care.

**Methods:**

*Community and Academic Synergy for Cancer Survivorship Care Delivery Enhancement* (Project CASCADE) is a theory-driven pragmatic hybrid trial testing implementation and effectiveness of a multi-component primary care-based survivorship care delivery intervention among 8 Texas CHC sites. The specific aims are: Aim 1: Implement a system-level cancer survivorship care delivery intervention in partnership with CHC clinicians, patients, and community representatives, which includes: (1) primary care clinician training in cancer survivorship care through provider-to-provider tele-mentoring, (2) identification and tracking of survivors by modifying existing clinic workflows, and (3) coordinating survivors’ care by designating a care coordinator champion. Practice facilitation and stakeholder engagement strategies will support intervention implementation; Aim 2: Test the effectiveness of the intervention on patient (screening for second primary cancers) and clinician outcomes (clinician knowledge of and confidence in survivorship care) using a stepped-wedge clinic-randomized design; and Aim 3: Evaluate implementation using a mixed-methods approach guided by the Practice Change Model. We will utilize electronic health record (EHR), survey, interview, and observation data to assess effectiveness and implementation outcomes.

**Discussion:**

Findings will inform a scalable, generalist primary care-based survivorship care model to enhance care delivery and outcomes in CHCs serving vulnerable populations. This study represents a critical step toward addressing gaps in cancer survivorship research and achieving equitable care for all survivors.

**Trial registration:**

This study is registered under clinical trial registration number NCT06883838; 2025–03-12.

**Supplementary Information:**

The online version contains supplementary material available at 10.1186/s12875-025-03108-1.

## Introduction

The US has over 18 million cancer survivors, projected to reach 22 million by 2030 [1]. Following the National Cancer Institute (NCI) and the American Cancer Society, “cancer survivors” are persons diagnosed with cancer no matter where they are in the course of their disease [2, 3]. The seminal Institute of Medicine Reports on “Delivering High Quality Cancer Care” and “Lost in Transition – From Cancer Patient to Cancer Survivor” published almost 18 years ago highlighted the complex healthcare needs of survivors and the challenges delivering coordinated healthcare [4, 5], 70% of cancer survivors also have other chronic conditions [6, 7] requiring management across multiple clinicians including oncologists, cardiologists, and primary care physicians. In 2025, we still lack effective and disseminatable solutions for optimizing delivery of high-quality survivorship care.

Most survivorship care models are based within academic health systems and cancer centers [8–12] and have shown mixed results of effectiveness and impact [13–15]. The growing population of cancer survivors, coupled with a projected shortage of oncology specialists [16], highlights the potential lack of sustainability of a survivorship care model led by oncology alone. Emerging primary care-based models, demonstrate a viable alternative [17–19]. Many cancer survivorship care services resemble care provided for chronic diseases such as diabetes, hypertension, and heart disease such as identifying and reducing risks related to sequelae of chronic conditions and its treatments, promoting healthy behaviors, and addressing behavioral health issues. Primary care practices have the care delivery processes, tools, and clinic staff for tracking and managing patients with multiple chronic conditions and complex health care needs, including sequelae of cancer and its treatments. Therefore, primary care is well suited to deliver whole person and coordinated survivorship care to survivors.

However, there are barriers to leveraging this capacity [20]. Primary care clinicians (PCCs) often do not feel equipped to care for survivor needs [21], lack knowledge about survivorship care guidelines [22–25], and need more experience recognizing and managing the adverse effects of cancer treatments [26]. In addition, there is a perception that cancer prevalence is low in primary care panels [27]. A study of 431 community health centers (CHCs) noted that 3% of adult patients had cancer documented in their electronic health record (EHR) [28]; this is likely an underestimate [28] because of inconsistent documentation. Our chart audit study in two CHC clinics identified 6.5% patients with ≥ 2 chronic conditions had cancer [29].

To address these gaps, *Community and Academic Synergy for Cancer Survivorship Care Delivery Enhancement* (Project CASCADE), a pragmatic, type 2 hybrid implementation-effectiveness trial in Texas-based primary care community health center (CHC) clinics, aims to:Implement a system-level cancer survivorship care delivery intervention in partnership with CHC clinicians, patients, and community representativesTest effectiveness of the intervention to improve patient and clinician outcomes using a stepped- wedge cluster-randomized trial designEvaluate implementation of the intervention using an iterative, concurrent mixed-methods approach guided by the Practice Change Model (PCM)

Accomplishing these aims will enhance the capacity of safety-net primary care teams to manage cancer survivorship in primary care, enabling survivors to receive coordinated, whole-person care.

## Methods

This study protocol adheres to The Standard Protocol Items: Recommendations for Interventional Trials (SPIRIT) guidelines (see supplementary file 1) [30]. Study results will be reported in adherence to the Consolidated Standards of Reporting Trials (CONSORT) guidelines [31] and the Standards for Reporting Implementation Studies (StaRI) guidelines [32]. In addition to publications, we plan to present results at scientific conferences and local community organization meetings.

### Study design

Project CASCADE is a pragmatic, Type II hybrid implementation-effectiveness trial using a cross-sectional, stepped wedge design coupled with a mixed-methods implementation evaluation. A stepped-wedge design is a type of constrained cluster-randomized trial in which groups (or clusters) of participants are sequentially randomized from a control condition to an intervention condition over multiple time periods [33, 34]. The key constraint is that randomization occurs only in one direction—from control to intervention condition. In this design, each cluster ultimately receives the intervention, and because data are collected over time, each cluster effectively serves as its own control. A Type II hybrid approach is ideal for this study as both intervention implementation and effectiveness are evaluated and have related study outcomes [35]. Stepped wedge designs are equitable by allowing for all clinics to receive the intervention [34, 36] at some point of time. In addition, we used the Pragmatic Explanatory Continuum Indicator Summary (PRECIS-2) to describe the parameters by which our study is pragmatic (Fig. 1) [37].

**Fig. 1 Fig1:**
[figure not shown]
Use of PRECIS-2 in Project CASCADE

### Setting

10 clinics spanning five CHC systems have agreed to participate in this study*.* These include FQHCs and community-oriented primary care clinics affiliated with county safety-net systems (Table 1). Per power estimations, only 8 clinics are needed to test effectiveness. We selected CHCs with a high proportion of minority and under/uninsured individuals. In addition, the CHCs vary in size (5–15 clinicians) and geographic location (urban–rural continuum), allowing us to examine contextual factors influencing effectiveness and implementation [38, 39].

**Table 1 Tab1:** Patient characteristics of partner CHCs

Community Health Center *(Partner Clinics)*	% Racial/Ethnic Minorities	% Uninsured/Medicaid	Estimated # Survivors seen per year per clinic*
CHC1 (2 clinics)	83%	53%	139
CHC2 (2 clinics)	98%	58%	106
CHC3 (2 clinics)	92%	77%	176
CHC4 (2 clinics)	91%	77%	607
CHC5 (2 clinics)	93%	88%	1008

^***^*Estimated prevalence of 6.5% based on preliminary data* [29]

### Participants

This system-level intervention will target clinic and clinic teams; patients will receive the intervention passively as part of the care they receive from their primary care teams. Eligible clinic team members include all employed clinicians (MD, DO, PA, NP) and clinic staff (e.g., social worker, medical assistant, care coordinator) of the participating CHC clinics. Eligible patients include current CHC patients that are at least 18 years old with a history of any type of cancer. This is an important pragmatic feature due to the strength of generalist primary care in prioritizing and delivering care for all conditions. An intervention focused on a single cancer is unlikely to be fully integrated into usual practice in community settings [27].

### Randomization procedures

We will randomize 8 CHC clinics in blocks of two every six months in a stepped-wedge design (Fig. 2). Each clinic team will implement the intervention over a 12-month period. The time before the intervention will serve as the usual care (control) condition, while the period during and after the intervention will constitute the treatment condition.

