### Quantitative data collection

#### EHR extraction/audit

The study team with support from clinic EHR specialists will extract EHR data for eligible patients at the end of every 6-month period. Extracts will include all patients with a history of cancer who were seen in the respective 6-month period.

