#### Power calculation

The primary outcome variable is continuous, for which Hussey and Hughes (2007) derived a closed-form analytical expression for power using linear mixed-effect model [34]. This formula is implemented in the PASS 2022 software, which is used for power calculation. From the historical records of recruitment feasibility, we propose to recruit 100 subjects (or more) per clinic in every six-month period. This results in a sample size N = 100*8*6 = 4800, out of which about 2000 will be under usual care and 2800 under intervention condition (excluding intervention implementation period in each clinic). We assume an ICC < 0.05 (within clinic association). We assume the difference in screening rate between intervention and usual care condition is ≥0.15 to guarantee ≥85% power, with a two-sided type-1 error of 0.05 (see power curve figure). Sample size using Heo et al. (2018) is slightly larger but still guarantees ≥ 80% power (checked using the swCRTdesign package in R software) [115]. A cross-sectional stepped wedge design assumes that outcomes are assessed for unique survivors every six months, and we recognize that eligible patients may return for regular clinic visits. However, for any eligible survivor, if the outcome of cancer screening in the past period is negative, then that past outcome does not affect the outcome of screening in the future period, and survivors who screened positive (in any period) are then not eligible for outcome assessment in future periods. The stepped-wedge design can be implemented in two forms: cross-sectional and repeated-measures. We have chosen a cross-sectional stepped-wedge design (open cohort), which assumes that clinics may evaluate new subjects during each observation window (i.e., every six months). While it is possible that a subject who screened negative in a previous period may return for screening in a later period (if still eligible), we expect the number of such repeat participants to be low. Importantly, for any given subject, a negative screening outcome in a previous period does not influence the likelihood of a positive outcome in a subsequent period. Subjects who screen positive in any period are referred for appropriate treatment and removed from future screening. Therefore, no sample size adjustment has been made for potential repeated observations within a clinic. Missing data is minimal in this cross-sectional design due to long-standing CHC relationships and ongoing partner engagement.

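### Clinic volumes differ 9.5-fold and no size restriction is stated, so the 2000/2800 split depends on the draw, and so does the power if the implementation year is excluded

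*Protocol article*

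**What the plan says.** All references are to the Protocol article.

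- **Randomization procedures:** "We will randomize 8 CHC clinics in blocks of two every six months in a stepped-wedge design". No stratification, pairing or constraint by size is stated. Implementation lasts 12 months, and the time during and after it counts as treatment.
- **Power calculation:** "we propose to recruit 100 subjects (or more) per clinic in every six-month period". The product 100 × 8 × 6 gives a total of 4800 patients, and the article divides this total as follows: "out of which about 2000 will be under usual care and 2800 under intervention condition (excluding intervention implementation period in each clinic"). The implementation period is outside the count here, whereas the randomisation section counts it as treatment. The claim is: "We assume the difference in screening rate between intervention and usual care condition is ≥0.15 to guarantee ≥85% power". The test is two-sided at the 5% level. On clustering: "We assume an ICC < 0.05 (within clinic association").
- **EHR extraction/audit:** "Extracts will include all patients with a history of cancer who were seen in the respective 6-month period". There is no cap.
- **Setting and Table 1:** ten clinics in five CHC systems agreed to take part. "Per power estimations, only 8 clinics are needed to test effectiveness", and the text does not say which eight. Estimated survivors per clinic per year are 139, 106, 176, 607 and 1008 for CHC1 to CHC5, with two clinics in each.
- **Data analysis:** the Hussey and Hughes model, with a random clinic effect and fixed period effects.

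**The concern.** The power calculation treats the eight clinics as interchangeable. The data rule and Table 1 say they are not: cell sizes will follow clinic volume. In a stepped wedge, a clinic's step fixes how many of its periods fall under each condition and which other clinics it can be compared with. If volumes differ widely and the draw takes no account of them, one random draw decides the patient split and possibly the precision of the primary test. It can also tie clinic volume, and with it CHC system, to calendar time.

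**Working it through.** **1. The plan's own figures.** With crossovers at periods 2 to 5 and two clinics per step, usual-care clinic-periods are 2 × (1+2+3+4) = 20 and intervention clinic-periods are 2 × (5+4+3+2) = 28. At 100 each this gives 2000 and 2800, as stated (42% usual care). The count is the same for six periods with implementation counted as treatment and for eight periods with two implementation periods dropped per clinic.

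**2. Volumes.** Halving Table 1 (an assumption) gives 69.5, 53, 88, 303.5 and 504 per six months. The ratio is 1008/106 = 9.5. The four CHC4 and CHC5 clinics hold 3230/4072 = 79% of survivors. Six of the ten clinics fall below 100, so at least four of any eight do.

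**3. Split.** A clinic of size m in step s contributes m·s usual-care and m·(6 − s) intervention patients.
- CHC5, CHC3, CHC1, CHC2 pairs in steps 1 to 4: 2 × (504 + 2×88 + 3×69.5 + 4×53) = 2201, out of 12 × 714.5 = 8574, or 26%.
- CHC2, CHC1, CHC3, CHC5 pairs in steps 1 to 4: 2 × (53 + 2×69.5 + 3×88 + 4×504) = 4944, out of 8574, or 58%.

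**4. Power.** Inputs are difference 0.15, two-sided 0.05, ICC 0.05 and total variance p(1 − p). The screening rate p is not given, so 50% and 30% are assumed. The generalised least squares variance under the Hussey and Hughes model was computed for all 6210 distinct allocations of eight of the ten clinics.

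| Implementation period | Equal clinics of 100 | Free draw: worst | Free draw: median | One large + one small per block: worst |
|---|---|---|---|---|
| Both six-month periods excluded, p = 50% | 79% | 58% | 87% | 96% |
| Both excluded, p = 30% | 86% | 66% | 92% | 98% |
| One six-month period excluded, p = 50% | 99% | 96% | >99% | at least 96% |
| Counted as treatment, p = 50% | >99% | >99% | >99% | >99% |

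Under full exclusion, about 43% (p = 50%) or 16% (p = 30%) of free draws fall below 85%. Keeping all four large clinics but placing them freely still leaves about 27% or 7% below. With pairing none does, and the usual-care share stays within 38% to 46%.

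**5. Why some draws are bad.** Under full exclusion, step 1 is observed in periods 1 and 4 to 8, and step 4 in periods 1 to 4, 7 and 8. Period 4 is the only period that holds both conditions: step 1 treated, step 4 in usual care. A hand check takes the step 1 minus step 4 difference in period 4, less its mean over periods 1, 7 and 8, where both share a condition. Its variance is σ²(1/n₁ + 1/n₄)(1 + 1/3), with σ² = 0.25 × 0.95 = 0.2375 and n the two-clinic total per period.
- Equal clinics, n = 200 and 200: SE 0.0563, 0.15/SE = 2.67, power 76% (full model 79%).
- CHC1 pair in step 1, CHC2 pair in step 4, n = 139 and 106: SE 0.0726, ratio 2.07, power 54% (full model 58%, the worst draw).
- A CHC2 and a CHC4 clinic in each of steps 1 and 4, n = 356.5 and 356.5: SE 0.0421, ratio 3.56, power 95% (full model 96%, the worst paired draw).

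The sizes in steps 1 and 4 therefore drive the result.

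**6. Sensitivity (p = 50%, full exclusion).** If six-month counts equalled the yearly ones, the minimum would be 86.5%, though repeat patients would then be common. With a clinic-by-period effect of 20% of the ICC, free draws give 40% to 67% and paired draws 53% to 60%.

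**The case against.** **The low power belongs to one layout.** The product 100 × 8 × 6 reads naturally as six periods, and the randomisation section's definition of treatment then yields 2000/2800 with power above 99% in every draw. Fig. 2, which would settle the layout, is not available here. This stands: a reader might infer that power can simply fall to about 60%, and the documents do not support that without the exclusion. On the other side, the power section does say that implementation is excluded. Full exclusion is also the only layout of the three that puts equal-clinic power near the stated 85%.

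**Much of the shortfall is due to the exclusion.** This also stands. At a 50% rate, equal clinics already give only 79%, so counting every draw below 85% charges that deficit to the allocation. Unequal volumes raise power in most draws.

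**Large clinics sitting together is not the cause.** A reader might infer that it is. But large pairs in steps 1 and 4 give nearly 100%, and large pairs in steps 2 and 3 about 59%. All four in steps 1 and 2, with the CHC4 pair in step 1 and the CHC3 pair in step 4, give n = 607 and 176 in the hand check: SE 0.0482, ratio 3.11, power 88%, above the 76% for equal clinics.

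**Silence is not a size-blind draw.** The article condenses a fuller protocol that may contain a restriction. All that can be said is that none is stated. The fixed split and the power claim are stated, however, and neither follows from the Table 1 volumes under the draw as described.

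**Other points.** The split is given as approximate, Table 1 rests on a flat 6.5% prevalence, and fixed period effects already adjust for calendar time. These are fair and limit the weight of the point.

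**Conclusion.** The point holds in conditional form. Under any handling of the implementation period, the uniform 100 per clinic-period conflicts with Table 1 and the extraction rule. The usual-care share can then lie anywhere from about 26% to 58%, too wide for a single 2000/2800 figure. If the full 12 months are excluded, power in the planned model also depends on the draw, with the worst case about 58% (rate 50%) or 66% (rate 30%). Part of the gap to 85% comes from the exclusion itself. If implementation counts as treatment, power is not at risk in that model, and size-balanced steps only balance volume over calendar time. The figures rest on halved yearly counts, ICC 0.05 and assumed screening rates.

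**What to change.** 1. Reconcile Randomization procedures and Power calculation on whether the implementation period is analysed.
2. In Power calculation, use the Table 1 volumes, state the assumed screening rate, and report the minimum power and the range of the split over the permitted allocations.
3. In Randomization procedures, keep all four CHC4 and CHC5 clinics among the eight. For blocks not yet started, assign one of them and one CHC1 to CHC3 clinic to each block, with each set randomised separately. Blocks already started stay as they are.

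If all four blocks can be paired, the worst case under full exclusion rises to about 96% or 98% in the planned model. The gain is much smaller if a clinic-by-period effect is present: from about 40% to 53% with the 20% component at a 50% rate. The cost is a new randomisation list and a rerun of the calculation, with no extra patients, visits or staff. The downside is fewer possible allocations, and sister clinics of one CHC could not share a block if the rule were applied to both volume groups. If the sponsor wants sister clinics close in time, they could be limited to adjacent blocks, where the CHC system has both clinics in the trial.

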**Fig. 2 Fig2:**
[figure not shown]
Project CASCADE stepped wedge design

### Conceptual frameworks

We will use the Practical, Robust, Implementation, and Sustainability Model (PRISM) [40] to guide the implementation of the intervention (Fig. 3). PRISM integrates key implementation and care delivery theories to enhance program implementation and sustainability. It identifies four key domains influencing intervention adoption and long-term success: intervention perspectives (usability, adaptability, and organizational readiness), recipient characteristics (leadership, staffing, patient demographics), external environment (policies, financial incentives, community resources), and implementation infrastructure (staffing, protocols, and support systems). PRISM emphasizes adaptability while addressing barriers to effective and equitable healthcare implementation. Figure 3 illustrates how PRISM is applied within Project CASCADE, highlighting the key contextual domains shaping intervention adoption, execution, and long-term impact.

